# Long-term cardio-vascular risk assessment in chronic kidney disease and kidney transplanted patients following SARS-COV-2 disease: protocol for multi-center observational match controlled trial

**DOI:** 10.1186/s12882-022-02809-4

**Published:** 2022-05-06

**Keywords:** SARS-CoV-2, Cardiovascular disease, Cardio-vascular risk, Chronic kidney disease, dialysis, Kidney transplant

## Abstract

**Background:**

The coronavirus disease (COVID-19) caused by the severe acute respiratory syndrome coronavirus 2 (SARS-CoV-2) produced a pandemic since March 2020 by affecting more than 243 million people with more than 5 million deaths globally. SARS-CoV-2 infection is produced by binding to angiotensin-converting enzyme, which among other sites is highly expressed in the endothelial cells of the blood vessels, pericytes and the heart, as well as in renal podocytes and proximal tubular epithelial cells. SARS-CoV-2 and cardiovascular disease (CVD) are interconnected by risk factors association with an increased incidence of the disease and by determining de novo cardiac complications. At the same time, COVID-19 disease can lead to acute kidney injury directly, or due to sepsis, multi-organ failure and shock. Therefore, the pre-existence of both CVD and chronic kidney disease (CKD) is linked with a higher risk of severe disease and worse prognosis.

**Methods:**

The main aim of this study is to assess the CV risk in a CKD (stage 3 to 5), dialysis and kidney transplanted population, following SARS-CoV-2 infection, with focus on the endothelial dysfunction as compared to a control group of matched patients. By using clinical evaluation, flow-mediated dilatation, carotid-femoral pulse wave velocity, intima-media thickness, echocardiographic parameters, lung ultrasound, bioimpedance spectroscopy and a series of novel biomarkers, the investigators will determine the long-term impact of this disease on CV and renal outcomes.

**Discussion:**

This study will address the challenges and implications in long-term CV sequeale of COVID-19 and focus on a better understanding of the underlying mechanisms and possible therapeutic options.

**Trial registration:**

Patient enrolment in the trial started in January 2021 and is expected to finish at the end of 2022. The study can be found on ClinicalTrials.gov database with NCT05125913 identifier.

Registered on 18 November 2021 - Retrospectively registered.

## Background

The coronavirus disease (COVID-19) caused by the severe acute respiratory syndrome coronavirus 2 (SARS-CoV-2) first emerged in early December 2019 and was declared a pandemic on March 2020 [1]. Since then, the SARS-CoV-2 continues to infect millions of individuals worldwide, with more than 243 million confirmed cases and up to 5 million deaths [2]. With nearly 35,707 new detected cases in the last 24 hours (at the time of writing, 26th of October 2021), as declared by World Health Organization (WHO), the SARS-CoV-2 pandemic revives, producing a cascade of diagnostic and therapeutic challenges.

SARS-CoV-2 infection is produced by binding to angiotensin-converting enzyme (ACE2), which among other sites is highly expressed in the endothelial cells of the blood vessels, pericytes and the heart, as well as in renal podocytes and proximal tubular epithelial cells. Of note, ACE2 RNA expression in the kidney is nearly 100-fold higher than that in the lungs [3]. Autopsy studies detected the presence of SARS-CoV-2 in both myocardium [4] and renal tissue [5], suggesting that COVID-19 profoundly influences the cardiovascular (CV) system and the kidneys and this may lead to long-termed cardio-pulmonary-renal consequences.

According to the COVID-19 global literature platform available on WHO website, there are 388,238 documents that cover more than 60 well-known scientific databases, such as Medline, Scopus, Web of Science, PubMed, Science Direct, etc. Nearly 845 studies were found using “cardiovascular” and “renal/kidney” keywords, which describe the effects on both systems among SARS-CoV-2 patients, even if it is acknowledged that clinical course of severe COVID-19 can impair rapidly from mild to critical with renal and heart diseases. Among these, we will mention an observational retrospective cohort study, published by Naser et al. [6] that evaluates the risk factors, predictions, and progression of acute kidney injury (AKI) in 353 hospitalized COVID-19 male patients from the BDF, Royal Medical Services in Bahrain. The detailed analysis of laboratory kidney function testing revealed that 168 patients (47.6%) developed different AKI stages. Furthermore, the AKI group showed elevated levels of inflammatory, cardiac injury, and fibrinolysis markers at time of admission, when compared with the non-AKI group. According to the author’s data upon admission, the potential predictors of AKI in COVID-19 are age, the frequencies of the comorbidity, diabetes, hypertension, chronic kidney disease (CKD), cardiovascular disease (CVD) and the severity of pneumonia. When analysing the recovery versus death rate for 87 deaths (51.8%) were recorded for AKI development in comparison to only 4 deaths (2.2%) for non-AKI group. It is important to remark that the authors did not make any suggestions regarding causal relationships between exposure and AKI, just recommending that clinicians should perform kidney function tests on admission and follow-up in hospitalized COVID-19 patients. In the Brazilian multi-center cohort study recently published, one in every five kidney transplant (KTx) patients died after being diagnosed with COVID-19, and the rate of death was significantly higher in those with AKI, mainly when renal replacement therapy was vital [7]. The study included 1680 KTx patients diagnosed with SARS-CoV-2 virus at 5,9 years after transplantation, from 35 Brazilian centres, from which 88.6% reported comorbidities, mainly hypertension, diabetes and CVD. In the call to action publication of the ERA-EDTA working group, CKD is defined as the most prevalent comorbidity for severe COVID-19, along with dialysis and organ transplantation, therefore several urgent action should be taken to prevent severe COVID-19 for this group of patients [8].

Another case report published by Chibane et al. [9] this year highlights that COVID-19 is associated with hyperacute multi-organ thromboembolic storm, existent at a 66-year old female patient admitted for pre-syncope, with post-mortem diagnosis of the infection. Transthoracic echocardiography evidenced pulmonary thromboembolism that was followed by an ischemic stroke and death, despite anticoagulation therapy. Therefore, the concept of coronavirus infection of endothelial cells and hypercoagulability could be supported, even in the absence of respiratory symptoms.

In June 2021, Rao et al. [10] published a large, multicenter, retrospective study that associates AKI with mortality in patients hospitalized with COVID-19, and demonstrates for the first time the relationship between AKI and CV events in COVID-19 for the hospitalization period. The American Heart Association’s (AHA) COVID-19 CVD registry enrolled 8574 patients with COVID-19 and CKD, end-stage kidney disease (ESKD) and AKI. According to multivariate adjustment, CKD and ESKD were not associated with mortality or major adverse cardiac events in the acute episode of SARS-CoV-2 infection, an unexpected finding given prior studies linking CKD with higher mortality in COVID-19 [11]. The authors explained the difference by the complexity of the data collection and multivariate models with extensive tuning for covariates.

As expected, COVID-19, the kidneys and the CV system are linked in a bidirectional way. On one hand, both CVD and renal disease represent a risk amplifier for morbi-mortality in the COVID-19 setting [12, 13]; on the other hand COVID-19 can exacerbate associated CVD and determine de novo cardiac complications (acute myocardial injury, stress cardiomyopathy, myocarditis, pericarditis, arrhythmias, heart failure and cardiogenic shock) [3, 12]. Furthermore, myocardial injury is also an important prognostic factor for the disease severity [14], as well as in-hospital and long-term mortality [14, 15]. At the same time, COVID-19 can lead to AKI directly, or due to sepsis, multi-organ failure and shock [3, 16].

More and more studies are reporting the persistence of COVID-19 related symptoms for more than a month after the acute episode, recently defined as post-COVID syndrome*.* The percentage of incessant symptomatology varies from 35 to 89.2% [17, 18] and it is independently associated with age [17], two or more comorbidities and the severity of the acute disease [18–21]. It looks that women are more predisposed to experience remaining symptoms [22]. The laboratory abnormalities are also frequently reported. An increase in D-dimer, interleukin-6 (IL-6), C-reactive protein (CRP), fibrinogen level as well as lymphocyte count may serve as predictors for long COVID [23]. The percentage of renal transplant recipients who survived acute COVID-19 and had no clinical symptoms or were free from any laboratory abnormalities after 2 months from the initial diagnosis was 11.53%. Sustained clinical symptoms were found in 45.2%, and one or more laboratory abnormalities were reported in 71.2%. Long-term complications in these patients were strongly predicted by diabetes mellitus, hospitalization in the acute setting, renal allograft function, as well as laboratory abnormalities [24].

COVID-19 survivors have higher risks of AKI, de novo development or worsening of proteinuria, eGFR decline and progression to ESKD. These outcomes are reported even among patients those with mild symptoms and increase with the severity of the infection [25].

The underlying mechanisms of these manifestations and long-term complications are not completely understood, but emerging data emphasize the endothelium, as a central pillar in the long COVID conundrum, with implications in inflammation, the pro-thrombotic phenotype and disseminated intravascular coagulation [26]. Endothelial dysfunction (ED) refers to a systemic condition in which the endothelium loses its physiological properties, including the tendency to promote vasodilation, fibrinolysis, and anti-aggregation [13]. Morphologic findings from deceased patients confirm the presence of viral elements within endothelial cells and an accumulation of inflammatory cells, with evidence of endothelial and inflammatory cell death. Endotheliitis in several organs as a direct consequence of viral involvement and of the host inflammatory response may explain the impaired microcirculatory function in different vascular beds and clinical sequelae in patients with COVID-19 [27].

In this context, the European Society of Cardiology recently stated the need for further research to elucidate the role of endothelium in COVID-19 and to assess the long-term CV effects following COVID-19 [26].

## Methods

Data emerging from the general population suggests that COVID-19 is essentially an endothelial disease, with possible deleterious long-term effects that are currently incompletely understood. Therefore, our aim is to assess the CV risk in a CKD, dialysis and KTx population, following SARS-CoV-2 infection, by determining the long-term impact of this disease on CV and renal outcomes in the aforementioned population as compared to a control group of matched patients (see Fig. 1).

**Fig. 1 Fig1:**
[figure not shown]
Protocol flowchart

### Objectives

The objectives of this observational study are to determine:the feasibility of flow mediated dilation (FMD), bioimpedance spectroscopy (BIS) fluid assessment, lung ultrasound (LUS) and pulse wave velocity (PWV) measurement in CKD patients following COVID-19 and matched CKD control-patients without a history of previous SARS-CoV-2 infection;the long-term impact of the COVID-19 on markers of CV risk and ED in patients with CKD and KTx on a composite CV outcome (time to first non-fatal myocardial infarction, non-fatal stroke, hospitalization for heart failure or CV death) and on all-cause mortality;the long-term impact of the COVID-19 on markers of CV risk and ED in patients with CKD and KTx on a composite renal outcome: doubling of creatinine or a 40% decline in eGFR or dialysis initiation.

### Study design

This observational cohort study will include CKD (stage 3 to 5), dialysis and KTx patients from dialysis unit’s auxiliary to Dr. C.I. Parhon University Hospital, Iasi, Romania, diagnosed with COVID-19 according to the interim guidelines of the WHO [28] using the reverse transcriptase polymerase chain reaction (RT-PCR) assay from nasal or throat swab. Patients from North-East of Romania with a documented history of SARS-CoV-2 will be recruited into the CARDIO SCARS IN CKD observational cohort study. All participants must have recovered from acute illness due to SARS-CoV-2 virus infection.

### Study population

We aim to enrol 250 patients, divided into two groups with minimum 125 patients per group: COVID group and non-COVID group. Both groups will be monitored at 6, 12 and 24 months since the first procedure visit, defined as the baseline.

#### Inclusion criteria

Age > 18 years;Patients with CKD stage 3–5, including dialysis or KTx with confirmed COVID-19, at minimum 2 weeks after the confirmed test;Age, sex and kidney disease (CKD stage 3–5, dialysis or KTx) matched patients without confirmed SARS-CoV-2 infection.

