#### Clinical data

Personal data (age, sex, height); CV risk factors (smoking, alcohol use, weight, body mass index); comorbidities (diabetes, hypertension, coronary artery disease, heart failure etc); physical examination (blood pressure, heart rate, crackles, pedal edema etc); type of renal disease; renal function (urea, creatinine, proteinuria, etc); medication; inflammation evaluation: CRP; complete blood count will be collected.

For the dialysis population: dialysis vintage and for the transplantation population: dialysis vintage before transplantation; date of transplantation, type (living or cadaveric donor), mismatch number, type of induction therapy; type of chronic immunosuppression therapy, will be also collected. Supplementary, for the COVID arm, we will assess also the severity of the infection, administered treatment, use of oxygen therapy, vaccination status.

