### Outcome data

***The primary outcomes of this study*** will be all-cause mortality rate, a composite CV outcome (time to first non-fatal myocardial infarction, non-fatal stroke, and hospitalization for heart failure or CV death) and long-term impact of the COVID-19 on markers of CV risk and ED in all included patients.

***Secondary outcomes*** are defined as a composite of renal outcome: doubling of creatinine or a 40% decline in eGFR or dialysis initiation in CKD or KTx patients.

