### Statistical analysis

The statistical analyses will be performed using the SPSS for Windows, version 19.0.1, R (version 3.1.2) package for statistical analysis and STATA 13. Non-normally distributed variables will be expressed as median with interquartile range and normally distributed variables as mean ± SD, as appropriate. Between-group comparisons will be assessed for nominal variables with the Chi-square test, and by Kruskal-Wallis test or one-way ANOVA for the rest of the variables. In order to comply with the assumptions for regression analysis, logarithmic conversion will be performed for non-normally distributed variables. Pearson correlation coefficient will be used to determine correlations between variables. Stepwise multivariate regression analysis including all univariate associates (*p* < 0.05) will be used to assess the independent associations between variables. Survival and time-to-event analysis of outcomes will be performed using Kaplan-Meier cumulative survival plots and Cox proportional hazards model, including adjustment for potential confounding factors. In the multivariate Cox models, we will adjust for all variables that will be correlated to the study outcomes with *P* < 0.05 at univariate Cox analyses.

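### Matching pools CKD stages 3, 4 and 5 into one class, and the covariate screen does not guarantee adjustment for baseline kidney function

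*Protocol article*

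**What the plan says.** The Inclusion criteria of the protocol article describe the comparison group as "Age, sex and kidney disease (CKD stage 3–5, dialysis or KTx) matched patients" who have no confirmed infection. That gives three matching factors: age, sex and kidney disease. The bracket lists three kidney categories, and the whole of CKD stage 3 to 5 is one of them. No other section matches on individual stage, on eGFR or on date.

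The secondary outcome, under Outcome data, is a renal composite: "doubling of creatinine or a 40% decline in eGFR or dialysis initiation in CKD or KTx patients".

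Under Statistical analysis, the Cox models will include adjustment for confounders, chosen by a screen: "we will adjust for all variables that will be correlated to the study outcomes with" P < 0.05 in univariate Cox analyses. The regression models are stepwise and start from covariates that pass the same univariate threshold. Baseline kidney function is not named as a covariate that stays in regardless. Renal function, including creatinine, is collected (Clinical data).

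On timing, the Trial registration section says "Patient enrolment in the trial started in January 2021 and is expected to finish at the end of 2022". Study population starts each patient's clock at that patient's own baseline: "Both groups will be monitored at 6, 12 and 24 months since the first procedure visit, defined as the baseline".

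**The concern.** A matched design should balance the strong determinants of outcome between the arms. For the renal composite, baseline kidney function is such a determinant almost by construction: one component is starting dialysis, and a stage 5 patient is nearer to that point than a stage 3 patient. Under the stated criterion these two patients are interchangeable. If the COVID group contains more advanced CKD than its controls, or the reverse, some of the between-arm difference reflects stage and not infection.

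The planned analysis does not close the gap with certainty. A significance screen can drop a real confounder when events are few. The planned Kaplan-Meier curves and simple group comparisons are unadjusted and would carry any imbalance in full.

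**Working it through.** **1. The plan's own figure.** Sample size power calculation gives 9% against 22% mortality, alpha 0.05 (taken as two-sided), power 80%, 125 per group. With p̄ = (0.09 + 0.22)/2 = 0.155:

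n = [1.960·√(2·0.155·0.845) + 0.842·√(0.09·0.91 + 0.22·0.78)]² / 0.13² = (1.003 + 0.424)² / 0.0169 ≈ 120.5, so 121 per group.

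Power at 125 per group is 81.4%. The stated figure reproduces, and this point does not affect it. Expected deaths are 125 × (0.09 + 0.22) = 38.75, about 39.

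**2. What the criterion permits.** The matching categories are {CKD 3–5}, {dialysis}, {KTx}. A stage 3 control and a stage 5 case of the same age and sex share all three factors, so the pair is valid.

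**3. What a stage imbalance could do.** The documents give no stage-specific risks and no stage mix, so every input here is an assumption. There is no COVID effect in either illustration.

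*Renal composite, non-dialysis CKD class.* Assume 24-month risks of 10% (stage 3), 30% (stage 4) and 70% (stage 5).
- Mix 35/40/25: 0.35×10 + 0.40×30 + 0.25×70 = 33.0%.
- Mix 50/35/15: 0.50×10 + 0.35×30 + 0.15×70 = 26.0%.
- Difference 7.0 points. The formula is linear in the shares, so half that shift in mix gives 3.5 points and equal mixes give 0.

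*Mortality, same class, stages 3 and 5 only.* Assume 5% in stage 3 and 15% to 25% in stage 5.
- Smallest case: 15% in stage 5, share of stage 5 50% against 40%. 0.5×15 + 0.5×5 = 10.0%; 0.4×15 + 0.6×5 = 9.0%. Difference 1.0 point, risk ratio 1.11.
- Largest case: 25% in stage 5, share 60% against 30%. 0.6×25 + 0.4×5 = 17.0%; 0.3×25 + 0.7×5 = 11.0%. Difference 6.0 points, risk ratio 1.55.
- Against the planned 13-point difference: 1/13 = 8% to 6/13 = 46%.

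If the non-dialysis class is a share w of each arm and the other classes are balanced, the whole-cohort mortality difference is w times these values. With w = 0.5 (assumed) it is 0.5 to 3.0 points.

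**4. How reliable the screen is.** For a two-level covariate split evenly, the Schoenfeld approximation gives the chance of passing P < 0.05 as Φ(√(D/4)·ln HR − 1.96). With D = 39 deaths, √(39/4) = 3.12.
- HR 1.5 (assumed): 3.12×0.405 − 1.96 = −0.69, about 24%.
- HR 2.0 (assumed): 3.12×0.693 − 1.96 = 0.20, about 58%.

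CKD stage varies only within the non-dialysis class, so fewer than 39 deaths inform it and the chances are lower for the same hazard ratio.

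**5. How many forced covariates the data can bear.** Five kidney classes (4 parameters), eight enrolment quarters (7) and COVID status (1) make 12 parameters: 38.75/12 ≈ 3.2 deaths each. Three kidney classes (2), continuous eGFR (1), one period term (1) and COVID status (1) make 5: 38.75/5 ≈ 7.8 deaths each, before any other covariate.

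**The case against.** The strongest defence is that the bracket may only restate which patients are eligible, since nearly the same words define the COVID group just before it. This is a condensed article that also gives no matching ratio or age tolerance, so finer matching rules may sit in the full protocol. That has some force. But the article does state its matching factors, and the plain reading makes stage 3 to 5 a single item. If exact stage is meant, the wording still needs correcting.

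Second, adjustment is planned and renal function is collected. A determinant as strong as stage in the renal illustration would probably pass the screen, and the adjusted bias would then be smaller than 7 points. This stands in part. The screen helps most when the effect is large and least for mortality with about 39 deaths, and it guarantees nothing.

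Third, a reader might infer that the arms will differ systematically in kidney function. The documents do not support this. Pooling permits mismatched pairs, but nothing shows that they will occur in one direction, and Screening and enrolment describes recruitment during routine clinic visits with no sign that cases and controls come from different parts of the stage range.

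Fourth, a reader might infer that cases and controls will be enrolled in different pandemic waves, up to 24 months apart. That gap is only the theoretical maximum of the enrolment window. No stated rule about dates is wrong; the article is simply silent, and the full protocol may cover it. What remains is a modest reason for a period term: vaccination status, which varies with calendar time, is listed only for the COVID arm ("Supplementary, for the COVID arm, we will assess also the severity of the infection, administered treatment, use of oxygen therapy, vaccination status"), so it cannot stand in for period in a between-arm model.

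**Conclusion.** The point holds in limited form. The criterion as written treats stages 3, 4 and 5 as equivalent, and the P < 0.05 screen does not secure adjustment for baseline kidney function. Confounding of the COVID contrast is possible, not demonstrated, and its direction is unknown. It matters most for the renal composite in non-dialysis CKD patients, a secondary outcome, and less for mortality.

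The range of about 1 to 7 points combines 1.0 to 6.0 points for mortality with 7.0 points for one renal scenario. All of it is before adjustment and rests on assumed risks and mixes. It should be read as a scale of what is possible, not as an expected bias. The calendar-time aspect is secondary and justifies a precaution only.

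**What to change.** **Controls still to be enrolled.** Reword the criterion to match on CKD stage 3, stage 4, stage 5 not on dialysis, dialysis, or KTx, with age and sex as now. Where feasible, enrol each control close in time to its case.

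**All patients, including those already enrolled, who cannot be re-matched.** Pre-specify as forced covariates in every between-arm model, whatever their univariate P value:
- baseline eGFR as a continuous term, together with kidney class. For COVID patients use the last stable value before infection where available, because the Background reports eGFR decline after COVID-19 and a post-infection value could absorb part of the effect under study. For controls use a comparable earlier stable value;
- one parsimonious enrolment-period term, linear or two-level, and not eight quarters.

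**Cost.** Stage 5 controls may take longer to find. The forced terms use a few parameters against about 39 expected deaths, so other covariates have to be few. Creatinine and the baseline visit date are already available; earlier stable creatinine values must be taken from existing records and will be missing for some patients.

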### Sample size power calculation

According to sample size power calculations, including 125 patients in each group will provide statistical power (alpha 0.05 and power 80%) for an estimated difference in the mortality rate of 9% [29] in the non-COVID group compared to 22% mortality in the COVID positive group [30–34].

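### Diabetes and existing CV disease are not matched, and the Cox models adjust for them only if they reach P < 0.05 univariately, an unreliable test with about 39 deaths

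*Protocol article*

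**What the plan says.** All references are to the protocol article.

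- **Matching.** Under Inclusion criteria, the controls are "Age, sex and kidney disease (CKD stage 3–5, dialysis or KTx) matched patients" without confirmed infection. No other matching factor is named.
- **Prognostic role.** The abstract's Background says "SARS-CoV-2 and cardiovascular disease (CVD) are interconnected by risk factors association with an increased incidence of the disease" and links pre-existing CV disease to a worse prognosis. The main Background calls CV disease an amplifier of morbidity and mortality in the COVID-19 setting. Of kidney transplant recipients who survived COVID-19 it says: "Long-term complications in these patients were strongly predicted by diabetes mellitus".
- **Data.** Clinical data lists "comorbidities (diabetes, hypertension, coronary artery disease, heart failure etc" among the items collected, so these factors are available as covariates.
- **Selection rule.** Statistical analysis promises adjustment for potential confounders in general terms and names none. It then says "In the multivariate Cox models, we will adjust for all variables that will be correlated to the study outcomes", with P < 0.05 in univariate Cox analysis as the criterion.
- **Size.** Sample size power calculation assumes a "mortality rate of 9% [29] in the non-COVID group compared to 22% mortality in the COVID positive group", "including 125 patients in each group".

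**The concern.** A factor that is not matched can be controlled only in the analysis. Here a univariate significance test decides whether it is controlled. How much a confounder distorts the COVID effect depends on its association with both group and outcome. Its univariate P value in one modest sample measures the second only noisily and is contaminated by the first. A prognostic factor that is commoner in the COVID group can fail the test, and its excess risk then stays in the COVID hazard ratio.

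The test is also repeated for each outcome. The mortality, CV and renal models may therefore end up with different adjustment sets, chosen after the data are seen, and their COVID effects would not be comparable.

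**Working it through.** **1. The plan's own figure.** Inputs: 9% and 22% mortality, alpha 0.05 (taken as two-sided), power 80%, 125 per group. The mean proportion is 0.155.

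n per group = [1.96 × √(2 × 0.155 × 0.845) + 0.8416 × √(0.09 × 0.91 + 0.22 × 0.78)]² / 0.13² = (1.003 + 0.424)² / 0.0169 ≈ 121.

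Power at 125 per group is 81.4%. The stated sample size is sound on its own assumptions.

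**2. Expected deaths.** 125 × 0.09 + 125 × 0.22 = 11.25 + 27.5 = 38.75, about 39. The implied COVID HR is ln(0.78)/ln(0.91) = 2.63.

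**3. Chance of passing the P < 0.05 test.** For a binary covariate with prevalence p, balanced between groups:

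Pass probability = Φ(√(39 × p(1−p)) × ln HR − 1.96).

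Example, p = 0.3 and HR 1.5: √8.19 × 0.405 − 1.96 = −0.80, so 21%.

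| Covariate HR | p = 0.2 | p = 0.3 | p = 0.4 | p = 0.5 |
|---|---|---|---|---|
| 1.5 | 17% | 21% | 24% | 24% |
| 2.0 | 41% | 51% | 56% | 58% |
| 2.5 | 63% | 75% | 80% | 82% |

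The pass rate reaches 50% at an HR of 2.19, 1.98, 1.90 and 1.87 respectively.

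**4. Allowing for imbalance.** A real confounder is unbalanced, and its univariate test then picks up part of the COVID effect. Log-rank tests were simulated on 250 patients (4,000 runs, mortality near 9% and 22%). With prevalence 45% in the COVID group and 30% in controls, the pass rate is 38% at HR 1.5, 70% at HR 2 and 87% at HR 2.5.

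Steps 3 and 4 together give miss rates of 62-83% at HR 1.5 and 30-59% at HR 2.

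**5. Bias from one omitted confounder.** Approximate factor = (1 + p₁(HR−1)) / (1 + p₀(HR−1)), with p₁ the prevalence in the COVID group and p₀ in controls. At 45% versus 30%:

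- HR 1.5: 1.225/1.15 = 1.065
- HR 2: 1.45/1.30 = 1.115

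Weighting on the log scale by the miss rates in step 4 (0.62 and 0.30) gives average factors of about 1.04 and 1.03 per confounder.

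**6. Bias under the rule compared with forced entry.** Cox simulations, 1,000 runs each, about 39 deaths; geometric mean COVID HR and root mean squared error (RMSE) of log HR. In the HR 1.8 cases the two confounders have prevalence 50% and 45% in the COVID group against 35% and 30% in controls.

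| Case | HR, rule | HR, forced | Ratio | RMSE, rule | RMSE, forced |
|---|---|---|---|---|---|
| Two confounders of HR 1.8, no COVID effect | 1.05 | 0.99 | 1.06 | 0.342 | 0.344 |
| Three confounders of HR 1.5, no COVID effect | 1.11 | 1.01 | 1.10 | 0.331 | 0.329 |
| Two confounders of HR 1.8, COVID HR 2.63 | 2.80 | 2.73 | 1.03 | 0.399 | 0.400 |

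Interval coverage with no COVID effect is 94.6% under both approaches in the first case, and 95.7% (rule) against 96.5% (forced) in the second.

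**7. Sampling error for scale.** exp(1.96 × 2/√39) ≈ 1.9, so the 95% interval spans roughly a factor of 1.9 either side of the estimate.

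**The case against.** The strongest reply is that the harm is small. A bias of 3-10% sits inside an interval running a factor of 1.9 either way. Forcing covariates in removes bias but adds variance, so RMSE and coverage barely change. That stands, and it limits the weight of the point. It does not justify the rule: the bias is systematic, whereas the extra variance shows in the interval.

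A second reply is that naming covariates belongs in an analysis plan. That would answer an article that was silent. This one prints a selection rule.

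A reader might also infer more than the document supports:

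- **That the rule will usually drop these factors.** The article gives no prevalence or HR. At HR 2 the pass rate exceeds 50% for prevalences of 30-50%, and it is higher under imbalance. The article itself calls diabetes a strong predictor.
- **That the article ties diabetes to being in the COVID group.** Its diabetes statements concern outcomes among patients who already had COVID-19. Only the abstract's sentence on incidence speaks to exposure, through unspecified risk factors.
- **That the low-power argument covers every outcome.** The 39 deaths concern mortality. No event count is given for the CV composite, where existing CV disease may pass more readily. The marker outcomes are continuous measurements on up to 250 patients.
- **That the undated comorbidity list is a defect.** A condensed article may leave such detail to the data collection form.

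**Conclusion.** The point holds in a limited form. Two prognostic factors that the article itself names are neither matched nor fixed in the Cox models, and the printed test is an unreliable way to admit them. With about 39 deaths it misses a confounder of HR 1.5 roughly 60-80% of the time and one of HR 2 roughly 30-60%. The consequence is a modest upward bias of about 3-10% in the COVID mortality HR compared with forced entry, with little effect on type I error or total error, and adjustment sets that may differ between outcomes.

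These sizes rest on assumed prevalences, HRs and imbalances, and on the planned death rates. Because Study design requires recovery from the acute illness, deaths could be fewer. At 9% in both groups there would be 22.5, and the pass rate at 30-50% prevalence falls to 14-16% at HR 1.5 and 33-38% at HR 2.

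This is worth correcting because the correction is cheap. It does not threaten the study's main conclusion.

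**What to change.** In Statistical analysis, replace the univariate P < 0.05 rule for the between-group Cox models with a short covariate set fixed in advance and entered regardless of P. The set is age, sex, kidney disease category, diabetes, and CV disease present before the index infection (before enrolment in controls). Use the same set for each outcome.

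With COVID group (1), age (1), sex (1), kidney category (2), diabetes (1) and CV disease (1), the model has 7 terms, or 39/7 ≈ 5.6 deaths per term. If that is judged too few, or fewer deaths occur, replace the covariates with one propensity score for COVID group built from the same variables.

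The cost is a sentence or two of analysis text, the classification of CV disease as present before the index date or not, and a slightly wider interval for the COVID HR.
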